## Abstract

**Background:**

Effective interventions are required to reduce alcohol consumption and its associated harms at the population level. Reducing the alcohol content of beverages has the potential to reduce alcohol consumption through non-conscious processes. Before implementing a randomised controlled trial (RCT) to assess the effect of alcohol strength on alcohol consumption, its feasibility needs to be established. This study aims to pilot a RCT and obtain data to estimate key parameters required when designing a RCT. These key parameters include the direction and size of the intervention effect, the efficacy and efficiency of the study processes and the rates of licenced premises recruitment, participant recruitment and attrition.

**Methods:**

A double-blind randomised controlled cross-over pilot trial comparing the number of units of reduced strength lager consumed and the number of units of regular strength lager consumed in a single drinking occasion within licenced premises in the UK.

Descriptive statistics will report the efficacy and efficiency of the study processes and the rates of licenced premises recruitment, participant recruitment and attrition. Mean and 95% confidence intervals will be used to compare the consumption of alcohol and the duration of participation in study sessions, between the intervention arm and the control arm. The mean and standard deviation of UK units of alcohol consumed will be used to calculate a sample size for a definitive RCT.

**Discussion:**

This is the first naturalistic experimental study to assess the effect of alcohol strength on alcohol consumption in a single drinking occasion within licenced premises. Results from this pilot study will establish the feasibility of, and inform key data parameters for, a larger scale study.

**Trial registration:**

The trial is registered in the American Economic Association (AEA) Randomised Controlled Trial (RCT) Registry as of 16 June 2017. The unique identifying number is AEARCTR-0002266.

## Background

Excessive alcohol consumption is a causal factor for many chronic health conditions, and it increases the risk of intentional and non-intentional harm through violence and injury [1, 2]. In 2015, there were 8758 avoidable deaths in the United Kingdom (UK) that were directly caused by alcohol [3]. A study with over 55,000 UK participants found that of the 69% who reported drinking alcohol, 27% reported drinking at levels that are classed as high risk [4]. Moreover, 2.5 million people who regularly drink alcohol report exceeding weekly alcohol thresholds in a single drinking occasion [5]. The financial burden of alcohol-related harm is estimated to annually cost UK society betwen 1.3 and 2.7% gross domestic product (GDP) [6].

The most effective alcohol harm prevention interventions may be those that target non-conscious processes and that are readily scalable to the population level [7–11]. These include interventions that alter the properties or placement of external stimuli, such as the strength of alcoholic products [10–12]. Such interventions could be particularly beneficial within licenced premises where individuals may not have direct access to information such as the strength of alcoholic products. For example, lager “taps” often display a brand logo but do not incorporate information about the strength of the product. Labelling drinks as lower in strength has been shown to increase the amount of alcohol consumed within a laboratory setting [13]. However, we propose that when information about alcohol strength is not forthcoming, such as when lager is purchased from the “tap”, most consumers will not consciously seek this information. Therefore, consumers cannot knowingly compensate for drinking lower strength alcohol. Reducing the alcohol content of popular lager products that are sold on “tap”, or in other situations where information about alcohol content is not readily available, may lead to a reduction in alcohol consumption. Interventions that utilise non-conscious processes have the added benefit of potentially reducing health inequalities as their recipients are not required to be health literate and numerate or have high-functioning cognition: lack of which are more prevalent with higher levels of deprivation [9, 14].

Reducing the alcohol content of drinks, thereby reducing the number of alcohol units each drink comprises, was proposed as a means to reduce alcohol consumption by the UK Coalition Government (2010–2015) as part of the Public Health Responsibility Deal (PHRD) [15]. Between 2011 and 2013, 1.3 billion UK units of alcohol were removed from the UK market by reductions in the alcohol content of beverages. This equates to the average strength of beer falling from 4.42 to 4.14% alcohol by volume (ABV) [16]. There is scope to further reduce the ABV of alcohol in the UK market, but to date, there is insufficient evidence that reducing the alcohol content of drinks reduces the number of alcohol units consumed.

There is a paucity of studies that assess the effect of the strength of alcohol on alcohol consumption within a naturalistic setting. Most studies of alcohol strength are strength discrimination studies. The majority of these are laboratory based [17–21] and one study was based within a mocked-up lounge in a community centre [22]. All but one incorporate beer, or beer and spirits, and a single study focuses on wine [20]. These studies all support the hypothesis that people cannot readily distinguish between alcoholic products of different strength, which indicates that there is potential to subconsciously alter alcohol consumption by altering the ABV of alcoholic products. An experiment with Canadian students found that participants reported similar levels of enjoyment and perceived intoxication after consuming an equivalent volume of lower strength lager and regular strength lager [23]. However, this study has numerous limitations: it used a small sample of male students, it was based within a classroom, and participants were restricted to the amount of alcohol they could consume. A more robust study that assessed the effect of the strength of beer and mixed spirit-based drinks on consumption supports the hypothesis that reducing the alcohol content of drinks does not lead to an increase in the volume of alcohol consumed, therefore reducing consumption [24]. There were also limitations in this study’s design, however, most notably that it was based within closed student fraternity parties comprising a single fraternity at one university in the United States of America (USA) [24].

High-quality research is warranted to assess the effect of alcohol strength on consumption within a naturalistic environment. Prior to a definitive randomised controlled trial (RCT), a pilot study is required to test feasibility and estimate key parameters for the RCT’s design. This study aims to determine the feasibility of a RCT, which would assess whether people consume fewer units of Bud Light lager 3.5% ABV (BL) compared to Becks lager 4.8% ABV (B) in a single drinking occasion within licenced premises. The intervention product, BL, is one of few mainstream lagers sold in the UK that is below 3.8% ABV, and it is reported to have retailed well since its UK launch in March 2017 [25]. Results of a taste discrimination experiment to establish a control product for the pilot trial concluded that, out of a range of mainstream regular strength lagers, B tasted the most similar to BL (unpublished observations: [name], [name] and [name]). To reduce confounding from difference in taste, BL and B were therefore chosen as the intervention and control products for the pilot trial.

The current study is defined as a randomised pilot trial, in accordance with Eldridge et al.’s conceptual framework for defining feasibility and pilot studies in preparation for a RCT [26]. That is, the future RCT, or parts of it, including the randomisation of participants, will be conducted on a smaller scale to see if it can be done. It could also legitimately be called a randomised feasibility study, but for clarity it will not be referred to as a feasibility study [27]. Additionally, and in line with Teare et al.’s definition of a pilot study, it will provide data with which to estimate key parameters for the design of a RCT [27]. It is an external pilot study: a stand-alone piece of work that has been planned and will be carried out independently to a main study [28].

## Methods/design

### Aim/objectives

The overall aim of the study is to pilot a double-blind randomised controlled cross-over trial to assess the effect of alcohol strength on alcohol consumption. The feasibility objectives are to establish whether:Components of the study protocol are efficient and work together or can be amended to be or do soA sufficient number of licenced premises can be recruited to host the studyThe participant recruitment rate per study session is sufficientParticipant retention is sufficientThe sample size derived from data obtained in the study is achievable for a future definitive trial.

The participant-centred objective is to establish whether:Estimations of the mean and 95% confidence intervals of the number of UK units of alcohol consumed by participants in a single drinking occasion support the hypothesis that people consume fewer UK units of alcohol when they consume reduced strength lager.

### Design

The study is a double-blind randomised controlled AB/BA cross-over pilot trial. The AB/BA cross-over design means that each participant experiences both the intervention and the control conditions, within a two-arm trial, on separate occasions and in a randomised order. There will be a four-week washout period between each participant´s study sessions, which is deemed adequate for participants to have desensitised to the sensory aspects of the alcohol they consumed in their first study session. There is no risk of carryover effects from the alcohol consumed during participants’ first study session, as alcohol is expelled from the body at the rate of approximately one unit per hour. There is a possibility of period effects as the characteristics of the participants may alter between their two study sessions: this will be tested for using a *t* test between the sequences AB and BA.

### Setting

The pilot trial will be based within on-trade licenced premises in the South East of England, and London, UK. For more information, refer to the “Recruitment of licenced premises” section.

### Participants

Fifty-two adults who regularly consume lager within licenced premises will be recruited for the pilot trial. See Table 1 for the Standard Protocol Items: Recommendations for Interventional Trials (SPIRIT).

**Table 1 Tab1:** Standard Protocol Items: Recommendations for Interventional Trials (SPIRIT) figure

Time point	Study period							
	Enrolment	Allocation	Post-allocation					Close-out
	≥ 24 h before study session 1	When participant arrives for study session 1	Study session 1	End of study session 1	When participant arrives for study session 2: 4 weeks after study session 1	Study session 2	End of study session 2	Approx 48 h after the final study session at the venue
Enrolment								
Eligibility screen	X							
Consent		X						
Allocation		X						
Interventions								
Bud Light			X			O		
Becks			O			X		
Assessments								
BrAC reading		X		X	X		X	
Time recorded		X		X	X		X	
UK units of alcohol consumed counted				X			X	
Questionnaire				X			X	
Debrief email/letter								X

Participants must meet all of the inclusion criteria and not meet any of the exclusion criteria (Table 2).

**Table 2 Tab2:** Inclusion/exclusion criteria

Inclusion	Exclusion
≥ 18 years old	Has ever sought help, or been treated, for an alcohol dependency
Regular drinker of lager within a licenced premises (≥ once in the past three months)	Has an illness or condition with which they should not be consuming alcohol
Able to attend two study sessions	Is on medication with which they should not be consuming alcohol
Provides informed consent	Pregnant
	Has a BAC > 35 μg/100 ml breath when they arrive for a study session

Figure 1 illustrates the participants’ pathways through the pilot trial.

**Fig. 1 Fig1:**
[figure not shown]
Participants’ pathways

### Interventions

#### Intervention product

The intervention product is Bud Light lager 3.5% ABV. It will be poured from 440-ml cans into a pint glass so that a full pint (568 ml) is served. Participants may consume the intervention product ad libitum during their study sessions.

#### Control product

The control product is Becks lager 4.8% ABV. It will be poured from 440-ml cans into a pint glass so that a full pint (568 ml) is served. Participants may consume the control product ad libitum during their study sessions.

#### Discontinuing or modifying intervention/control products

The intervention and control products will not be replaced or modified during the pilot trial.

### Outcome measures

The primary outcome is the feasibility of a RCT. A RCT would be deemed feasible if it adheres to the following points:Components of the study protocol are efficient and work together or can be amended to be or do so. These include:The administration of data collection toolsThe consent processThe randomisation processData management processesThe roles and requirements of study personnelThe licenced premise recruitment rate is a minimum of one per month for a minimum of 4 months or until four licenced premises have been recruited.Participant recruitment rate is a minimum of four per study session.The rate of attrition for the pilot trial is less than or equal to 30%, and this does not vary by more than 10% according to the arm of the trial.The sample size is achievable to obtain within a year based on the recruitment rate of licenced premises and participants.

In addition, one participant-centred outcome will be assessed:Whether estimations of the mean and 95% confidence intervals of the number of UK units of alcohol consumed by participants in a single drinking occasion, when they consume BL and B, suggest that people consume fewer UK units of alcohol when they consume reduced strength lager.

### Sample size

As there are no data from previous studies on which to base a statistical calculation, and there is no consensus in the literature about the required sample size for pilot trials, the sample size has been calculated using preliminary datasets. These preliminary datasets are based on the hypothesis that there is no significant difference between the number of alcoholic drinks individuals consume, regardless of their ABV, which has been shown in a previous study [24].

Firstly, preliminary datasets were created for 40 patrons at each of four different licenced premises with different demographics, based on their average patron’s characteristics, i.e. age and gender. The mean patrons’ age was calculated from each licenced premises’ preliminary dataset. Mean age was used to estimate the number of units that each of the 40 hypothetical patrons would consume under normal conditions, based on age-related population data for alcohol consumption [29]. The estimated number of units consumed under normal conditions was reduced by 27% to give the estimated number of units consumed under the intervention: the difference in ABV between BL and B is − 27%. Estimated mean units and SD for units consumed from BL and B were calculated; a conservative estimate for SD in the intervention arm was used: the same SD as in the control arm. Where the licenced premises’ population incorporated a higher proportion of male to female consumers, this was accounted for in the calculations and the mean consumption increased accordingly. From these data, the estimated mean difference and SD of the mean difference of UK units of alcohol consumed were calculated. These data enabled delta to be calculated, 0.3977.

Preliminary data for the licenced premises with the largest SD was used to calculate the sample size using the Rstudio software ‘R Stats Package’ and the function power.t.test [30]: this provided the most conservative calculation of sample size. The figures that were inputted into Rstudio were alpha = 0.05, beta (power) = 0.8, delta = 0.3977, SD = 1. The sample size for a two-sided paired *t* test was calculated as 52: 52 participants participating in two trial arms. As this does not account for attrition, participants who drop out of the pilot trial will be replaced.

#### Trial withdrawal

Participants who wish to withdraw from the study will be directed to contact the PI via email or telephone or express this to the PI verbally during a study session.

Participants who are seen by the PI, the RA or the BP to be obviously and persistently breaching the protocol will be withdrawn from the study. These breaches include consuming any alcohol other than the study-specific lager which they have purchased, supplying non-participants with study-specific drinks, and disposing of any study-specific lager without declaring it.

#### Definition of end of study

The study will officially end when the final participant has been sent a debrief email/letter. If the pilot trial is deemed to be eliciting too many adverse events, then the University Research Ethics Committee (UREC) Chairperson may terminate it early.

### Recruitment

#### Recruitment of licenced premises

All licenced premises are eligible to participate regardless of whether they function under a premises licence or a club premises certificate.

A minimum of one and maximum of six licenced premises will be recruited via posts on Facebook and Twitter; blogs on scientific forums; local newspaper, magazine and radio advertisements; PI’s presentations at local Pubwatch meetings; targeted emails to licenced premises managers; and word of mouth. Recruitment will work on a first come, first served basis.

Managers of licenced premises that contact the PI with an expression of interest will be sent further details of the study by email or post. If they wish to proceed thereafter, then a meeting will be arranged between the premises manager and the PI. If the PI regards the venue as suitable to host the study, and the premises manager wishes to proceed, both parties will agree on the dates and times for a minimum of four study sessions. During study sessions, the licenced premises will still be open to the public. The licenced premises manager will sign a letter of agreement for research access.

#### Recruitment of participants

Fifty-two participants will be recruited through posts on the licenced premises social media accounts and through placing flyers and posters within the premises.

The recruitment advertisements will ask people who are interested to contact the PI via email or telephone. Once a potential participant has contacted the PI, they will be sent an invitation to participate in the study, a participant information sheet (PIS) and a link to an online eligibility survey. By default, these documents will be sent electronically. The documents will be sent through the post upon request with a stamped addressed envelope.

Recruitment will commence two months before the initial study session at each participating licenced premises.

Recruitment will continue until the sample size (*n* = 52) has been reached.

Recruitment will be monitored by the PI. The PI will stop recruiting at a participating licenced premises if either:The manager of the licenced premises expresses they do not wish for any more study sessions to take place (after the agreed four sessions)The licenced premises is failing to yield participants at an adequate rate: less than four per study sessionIt is no longer feasible for the licenced premises to host the study

The PI may recruit from multiple participating licenced premises at any one time, and this will be at their discretion.

#### Screening

Potential participants will be screened to assess their eligibility by completing an electronic survey using Qualtrics software. The survey will be sent through the post with a stamped addressed envelope upon request.

The PI will analyse the survey responses and contact those who are eligible to arrange two study sessions. Study sessions will be a month apart, on the same day of the week and at the same start time.

Those who do not fulfil the eligibility criteria will be sent an email or letter to thank them for expressing an interest in the study and explaining the reason why they are not eligible.

#### Consent procedure

When potential participants leave their contact details at the end of the electronic screening survey, they consent to their contact details being made available to the research team and for them to be contacted in relation to the study at any given time.

Individuals will take a breathalyser test when they arrive for their first study session and those whose breath alcohol concentration (BrAC) is equal to or below the UK’s drink-drive limit, of ≤ 35 μg/100 ml breath, will be asked to complete a consent form. If the individual’s BrAC exceeds this level, they will be told they cannot take part in the study during the current session as they may be too intoxicated to give informed consent.

Potential participants will be given the time they require to read the consent form (or have it read to them by the PI), ask any questions and complete the form. They will have received the PIS at least 48 h before their study session, so their consent will be regarded as fully informed.

### Allocation

#### Sequence generation

Participants will be randomly assigned to the order that they receive BL and B, using the AB/BA format, therefore counterbalancing conditions. A separate computer-generated randomisation sequence will be produced for each study venue using Randomization.com software [31].

#### Concealment

The first “treatment” label (pink or purple) designated to each subject in the randomisation sequence will be translated as a discrete, coloured label on a randomisation card that will be concealed in a sealed and numbered opaque envelope. The sealed envelopes will be placed in a pile, which will be overturned and placed within a box once all envelopes are present so that the sequence is in ascending numerical order.

#### Blinding

The participants and the RA will be blinded to the intervention and control products and the order in which they are assigned. Due to limited study personnel, the PI cannot be blinded.

Randomisation cards will display a colour-coded label, and the participants and the RA will be unaware of the colour-coding system. Coloured labels will be placed on the de-identified lager cans that will correspond to the coloured labels on the randomisation cards. The RA will ask the participants to show their randomisation card when they purchase a study-specific drink, and the colour of the label on the card will inform the RA which drink to serve.

#### Emergency un-blinding

In exceptional circumstances, whereby the participant’s welfare would be compromised without the disclosure of the alcohol product that they have consumed, the participant and any other relevant persons will be un-blinded to the intervention and/or control. Participants who are un-blinded will be removed from the study. The PI will report all disclosures to the CI.

### Data collection methods

#### Baseline measures

Participants’ BrACs will be measured at the start of each of their study sessions with an Alcosense Pro Fuel Cell Digital Breathalyser, using a one-way valve mouthpiece. The breathalyser is accurate to − 0.00‰ BrAC, + 0.1‰ BrAC, and will be calibrated annually by Alcosense [32].

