#### Data collection methods

The PI will maintain up-to-date records that cover point 1 in the “Outcome measures” section. Feedback from members of the research team, participating licenced premises and participants will be obtained and recorded throughout the study.

Electronic datasets will be created in Excel to monitor:Licenced premises that are approached by the PILandlords/managers who express willingness to participateLandlords/managers who sign a letter of accessParticipants who consent to participate (and at each separate participating licenced premises)Participants who consent and do not complete two study sessionsParticipants who consent and drop out during or after the intervention study sessionParticipants who consent and drop out during or after the control study session

To track the number of study-specific drinks served, the RA will stamp the participant’s randomisation card each time they are supplied with a fresh drink. The randomisation card will be handed to the PI at the end of each study session.

Participants will be briefed that if they do not consume the entirety of a study-specific drink they should return their drinking vessel to the RA. The RA will alert the PI who will measure the amount of alcohol that has been left in the vessel. The PI will quantify, in UK units, the amount of alcohol that each participant has left throughout each study session and deduct this from the number of UK units of alcohol served to each participant, which will be calculated by the PI. The number of UK units of alcohol will be converted to, and additionally displayed as, grams of alcohol for an international audience.

The PI will also record the times at which each participant commences and concludes each of their study sessions. This will enable a comparison between the duration of participants’ study sessions under each of the study conditions, which will indicate whether participants may be concluding their study sessions and then consuming non-study drinks.

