### Data analysis

The efficacy and efficiency of the study processes and the rates of licenced premises recruitment, participant recruitment and attrition will be analysed and reported using descriptive statistics.

Mean value and 95% confidence intervals will be used to compare the number of UK units of alcohol consumed and the mean duration of participation in study sessions, between the intervention arm and the control arm.

The mean and SD of the number of UK units of alcohol consumed will be used to calculate a sample size for future, larger scale studies. The components of the sample size calculation will be delta (mean difference/SD of mean difference) = derived from a calculation of the data, alpha (sig.level) = 0.05, beta (power) = 0.8.

A *t* test, between the sequences AB and BA, will be undertaken to test for a period effect.

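### Arrival breath alcohol is measured at both sessions and gates entry, but the stated comparison of units and the SD carried to the definitive trial make no use of it

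*Protocol article*

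**What the plan says.** **Entry.** Table 2 (Participants) excludes anyone who "Has a BAC > 35 μg/100 ml breath when they arrive for a study session". The Consent procedure describes the same gate for the first session: those "equal to or below the UK’s drink-drive limit, of ≤ 35 μg/100 ml breath, will be asked to complete a consent form", while above the limit "they will be told they cannot take part in the study during the current session as they may be too intoxicated to give informed consent". Arriving with some alcohol on board is therefore allowed.

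**Measurement.** Under Baseline measures, "BrACs will be measured at the start of each of their study sessions with an Alcosense Pro Fuel Cell Digital Breathalyser". Table 1 also schedules a reading at the end of each session, which makes four per participant.

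**Outcome.** Under Data collection methods, the PI will work out the units left undrunk and "deduct this from the number of UK units of alcohol served to each participant, which will be calculated by the PI". Alcohol drunk before arrival is outside this count.

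**Analysis.** Under Data analysis, "Mean value and 95% confidence intervals will be used to compare the number of UK units of alcohol consumed". That section also gives a t test between sequences for a period effect, and a sample size for later studies built from the mean difference divided by its SD. Neither it nor Outcome measures mentions BrAC.

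**The concern.** A cross-over removes differences between people. What is left in the paired difference is variation within a person from one session to the next, and drinking before arrival is a factor of that kind. Someone may arrive sober once and close to the limit the other time, and the two amounts of study lager then bought may differ for that reason as well as because of the product.

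The authors take session-level influences seriously elsewhere. Both sessions share a weekday and start time (Screening), and the one-month gap is meant to control for payday (Retention of participants). Arrival BrAC is a direct session-level measure, taken before any study lager is served in that session, yet the stated comparison leaves it out.

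Two outputs are affected. One is the single participant-centred estimate. The other is the SD of the paired difference, which feeds the definitive sample size and so the feasibility criterion that this size be achievable within a year. The end-of-session readings have no stated use at all.

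**Working it through.** **Inputs from the protocol (Sample size):** alpha 0.05 two-sided, power 0.8, delta 0.3977, SD 1, paired t test, n = 52.

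**Input not in the protocol:** r, the correlation between a participant's between-session difference in arrival BrAC and the same participant's difference in units. It is assumed, over the range 0 to 0.5.

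**Step 1. Reproduce the planned figure.** For a paired t test the noncentrality is delta × √n / SD on n − 1 degrees of freedom. Solving for power 0.8 gives n = 51.58, rounded up to 52; power at 52 is 0.803. The stated 52 is correct.

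**Step 2. Effect of adjustment if SD = 1 already contains the pre-drinking variation.** The residual SD of the paired difference is SD × √(1 − r²). Using this in Step 1:

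| r (assumed) | Residual SD | CI narrower by | n for 80% power | Power at 52 |
|---|---|---|---|---|
| 0 | 1.000 | 0% | 52 | 0.803 |
| 0.1 | 0.995 | 0.5% | 52 | 0.807 |
| 0.2 | 0.980 | 2% | 50 | 0.819 |
| 0.3 | 0.954 | 5% | 48 | 0.839 |
| 0.4 | 0.917 | 8% | 44 | 0.866 |
| 0.5 | 0.866 | 13% | 40 | 0.901 |

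Charging the one degree of freedom spent on the covariate (n − 2 in place of n − 1) changes no sample size in the table, and no power by more than 0.0003.

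**Step 3. If instead the pre-drinking variation comes on top of SD = 1.** The planning SD was built from age-related population data, so it may not include it. With SD = √(1 + v) and n held at 52:

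| Extra variance v (assumed) | Power at 52 | n for 80% power |
|---|---|---|
| 5% | 0.784 | 55 |
| 10% | 0.765 | 57 |
| 20% | 0.729 | 62 |
| 30% | 0.694 | 67 |

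**Step 4. Scale of the permitted range (illustration only).** Assume a blood:breath ratio of 2100 to 2300 and Widmark factors of 0.68 (80 kg man) and 0.55 (65 kg woman).
- 35 μg/100 ml breath = 0.00035 g/L; × 2100 to 2300 = 0.735 to 0.805 g/L.
- Man: × 80 × 0.68 = 40.0 to 43.8 g; at 8 g per unit, 5.0 to 5.5 units.
- Woman: × 65 × 0.55 = 26.3 to 28.8 g; 3.3 to 3.6 units.
- Product contrast per pint: 0.568 × 4.8 − 0.568 × 3.5 = 2.73 − 1.99 = 0.74 unit. Over the four pints per participant used to plan stock: 4 × 0.568 × 1.3 = 2.95 units.
- Arrival at the limit is thus 3.3/2.95 = 1.1 to 5.5/2.95 = 1.9 times the four-pint contrast.

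These are units in the body at the extreme of what is allowed. They are not units of change in study lager bought, and the protocol does not say how often anyone arrives near the limit.

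**The case against.** **Covariates belong in an analysis plan.** The article is condensed, states nothing false about BrAC and does not rule out adjustment. This has weight, and silence alone would not be a finding. But the article does state its comparison and the exact ingredients of the future sample size, and it explains why session times are recorded. Replacing a stated unadjusted comparison with one that uses a baseline already in hand is a specific improvement to what is written. The objection limits how strongly the point can be put; it does not remove it.

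**The design already deals with it.** "Participants will be randomly assigned to the order that they receive BL and B, using the AB/BA format", the comparison is within person, and weekday and start time are fixed. A reader might infer that unequal pre-drinking biases the comparison of products. The documents do not support that: with randomised order the imbalance is zero in expectation, and chance imbalance is part of what the confidence interval expresses. Only the precision argument stands.

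**The reading is used.** A reader might infer that it is collected and ignored. It is not: it decides who may consent and take part.

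**The unadjusted SD is a valid planning input.** This is right if the definitive trial keeps the same setting and does not adjust. Sizing that trial on a residual SD would then make it too small.

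**The covariate is imperfect.** Baseline measures gives a device error of up to +0.1‰. Read as 0.1 g/L against 0.735 to 0.805 g/L at the limit, that is 12 to 14% of the permitted range, and a difference of two readings carries the error twice. This makes a high r less likely.

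**BrAC is not the only check on recorded units.** Staff stamp every drink, leftovers are measured and session duration is compared. The rise in BrAC also depends on elapsed time, as the protocol's own elimination rate of about one unit per hour implies. It can support the count but cannot validate it.

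**Conclusion.** The point holds as one of efficiency. Arrival BrAC may be anything up to 35 μg/100 ml and is recorded at both sessions, but beyond the entry gate it plays no part in the stated comparison of units or in the SD carried forward. The cost is within-person noise and chance imbalance.

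Its size cannot be fixed from the document. If the planning SD already includes this variation, adjustment gains 2% of interval width or less for r up to 0.2, about 5% at r = 0.3 and about 13% at r = 0.5, where about 40 pairs would do the work of 52. At r = 0 there is no gain.

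It is tempting to set the alcohol on board at the limit against the contrast of a single pint, or to say that one person's difference could be mostly pre-drinking. Neither is supported. The first compares an extreme with one drink, where stock is planned on four. The second needs nearly one-for-one substitution of earlier drinking for study lager, on which the protocol gives no evidence.

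The primary outcome is feasibility, and the planned 52 is not in question. What is affected is the participant-centred estimate and the sample size derived for the definitive trial.

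**What to change.** In Data analysis:

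1. Keep the unadjusted mean difference in units (Bud Light minus Becks) with its 95% confidence interval. Beside it, give an estimate from a regression of each participant's difference in units on the difference in arrival BrAC (Bud Light session minus Becks session). The intercept is the product difference at equal arrival BrAC. Since the covariate precedes serving in each session, and the protocol takes carryover to be absent, adjustment should not absorb the product effect.
2. Report both the unadjusted SD of the paired difference and the residual SD. Use the residual SD for the definitive sample size only if that trial will make the same adjustment; otherwise use the unadjusted one.
3. Tabulate arrival BrAC and the arrival-to-end change by product, beside recorded units and session duration, and label it a rough check, because the change also reflects elapsed time and device error.

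The cost is one degree of freedom and one table. All four readings are already scheduled in Table 1.
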